### Sample size

An anonymized cohort consisting of patients who received chemotherapy following curative surgery for early stage breast cancer (stage I-III) between January 1, 2007 and December 31, 2009 in Ontario, Canada was identified using the Ontario Cancer Registry (OCR) at the Institute for Clinical Evaluative Sciences (ICES), and used for the sample size calculation. Details of this methodology have been published previously [2]. Associations between the number of ED + H visits and centre, age, number of women treated, duration of chemotherapy and type of chemotherapy, were evaluated. We estimated that 20 of these institutions provide adjuvant therapy to at least 50 breast cancer patients annually and would agree to participate.

Two different simulation approaches were used to determine the sample size for the cRCT: (1) assuming an over-disperse Poisson model (negative binomial distribution) and using summary data from the 2007–2009 ICES cohort, we selected the top 25 cancer treatment centres by patient volume (top-25 cohort) to maintain estimate stability; and (2) using the actual data from the cohort and randomly allocating the 20 largest centres equally to control or treatment arm within 5 strata based on the number of women treated at each centre. With the first model-based approach, we applied a design effect to the number calculated assuming independence. The intra-class correlation for the top-25 cohort was estimated at 0.028. In the second actual data approach, we reduced the observed visits by a fixed pre-specified percentage ranging from 20 to 40%.

Both approaches resulted in similar estimates. With approximately 73 women per centre (total sample size, 1460) from 20 centres, we would achieve 80% power to detect a 33% reduction in the number of ED + H visits, with a one-sided alpha = 2.5%. For the secondary patient-reported outcomes sub-study (PRO sub-study), at least 25 patients per centre (total sample size: 500) need to be enrolled for 80% power (one-sided alpha = 2.5%) to detect a treatment effect size of 0.35 standard deviations.

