### Cluster randomization

A covariate constraint-based randomization methodology proposed by Moulton [21] was used to randomly allocate the 20 participating centres to either intervention arm or control arm using a healthcare administrative dataset for early stage breast cancer patients diagnosed between January 1, 2010 and June 30, 2013 who received either adjuvant or neoadjuvant chemotherapy. The approach of Sismanidis et al. [22] was used to define the measure of imbalance in choosing the optimal allocation scheme. In brief, centres were grouped by the average ED + H visits per patient resulting in 14,000 unique unrestricted arrangements to force balance between the strata. Additional covariate-adjusted restrictions were applied to the groupings to achieve the acceptable mean difference between groups. One allocation scheme is then selected at random among all possible randomizations that achieve the best possible balance among the intervention arm and control arms followed by random assignment of study arms. Covariates considered in the model included patient volume, acute care visits, Charlson comorbidities, rurality, stage, regimen, facility type, nursing model, proportion of non-English speaking patients.

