### Statistical analysis

A comparison between the control and intervention arms (10 clusters in each group; approximately 730 patients per arm) will be undertaken using a randomization test for the risk and rate differences which will take into account the restricted randomization. In addition, 95% confidence intervals for the differences will be calculated based on the randomization distribution. As a supportive analysis, the intervention and control groups also will be compared using Negative Binomial mixed effects regression modeling where we will consider the impact of patient-level baseline covariates, such as age, stage, comorbidities, socioeconomic status and treatment regimen, on the intervention effect. The at-risk period will be from the first day of chemotherapy until 30 days after the last treatment. Patient reported outcomes will be assessed using general linear mixed models to adjust for clustering of the individuals within centres and the between-centre variation and assess the impact of the intervention alone, and after adjusting for important patient-level baseline covariates. Multiple imputation within centres will be used to account for missed assessments.

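### The supportive negative binomial model omits the centre's historical ED + H rate used to group centres for allocation, so its interval is too wide if that rate is prognostic

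*Protocol article*

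**What the plan says.** Under Cluster randomization, the allocation used administrative data on "early stage breast cancer patients diagnosed between January 1, 2010 and June 30, 2013". From these data "centres were grouped by the average ED + H visits per patient resulting in 14,000 unique unrestricted arrangements", and further restrictions were then applied. "Covariates considered in the model included patient volume, acute care visits, Charlson comorbidities, rurality, stage, regimen, facility type, nursing model" and the share of patients who do not speak English.

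Under Statistical analysis, the primary comparison ("10 clusters in each group; approximately 730 patients per arm") is a "randomization test for the risk and rate differences which will take into account the restricted randomization", and "95% confidence intervals for the differences will be calculated based on the randomization distribution". A negative binomial mixed model is added as a supportive analysis, in which "we will consider the impact of patient-level baseline covariates, such as age, stage, comorbidities, socioeconomic status and treatment regimen, on the intervention effect".

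**The concern.** Grouping centres on a prognostic variable makes the arms alike on it, so the arm difference varies less over the allocations that could have been drawn. A mixed model without that variable does not see this. The variance explained by the historical rate stays in the centre random effect and enters the standard error of the treatment effect. The interval is then wider than the design warrants, and the test rejects too seldom under the null.

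The supportive model is there to corroborate the primary result. Without the rate, it could give a clearly wider interval than the restricted randomization test on the same data, and so appear to cast doubt on a real effect for an avoidable reason.

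**Working it through.** **Inputs.** Sample size section: "With approximately 73 women per centre (total sample size, 1460) from 20 centres", with an intra-class correlation of 0.028. Cluster randomization section: 14,000 arrangements after grouping on the historical rate. Not in the protocol, hence assumed: the correlation r between a centre's historical and true trial-period rates (varied from 0 to 0.9), and how tightly the final scheme balances the rate.

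**1. The 14,000 arrangements.** C(8,4) × C(6,3) × C(6,3) = 70 × 20 × 20 = 28,000. Counting a split and its mirror image once, because arms are assigned afterwards, gives 28,000 / 2 = 14,000. This fits three rate groups of 8, 6 and 6 centres. The group sizes are an inference.

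**2. The plan's own power figure.** Design effect 1 + 72 × 0.028 = 3.016; 730 / 3.016 = 242 effective patients per arm. On the log rate ratio, with variance (1/μ + 1/(0.67μ) + 2k)/242, 80% power for a 33% reduction is reached at, for example, control mean μ = 0.6 with dispersion k = 0.40, 0.8 with 0.92, or 1.0 with 1.23. Neither μ nor k is stated, so the figure is plausible but cannot be reproduced uniquely. The point does not depend on it.

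**3. Between-centre share.** In units of total variance, a centre mean has between-centre variance 0.028 and sampling variance 0.972 / 73 = 0.0133. The share is 73 × 0.028 / 3.016 = 0.678.

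**4. Expected gain.** The historical rate explains 0.678 r² of the variance of centre means, so the standard error with the rate, relative to without, is √(1 − 0.678 r²):

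- r = 0.5: √(1 − 0.169) = 0.911
- r = 0.7: √(1 − 0.332) = 0.817
- r = 0.9: √(1 − 0.549) = 0.672

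With t quantiles on 17 rather than 18 degrees of freedom, the width ratios are 1.004 (r = 0), 0.915, 0.821 and 0.674.

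**5. Simulation of the supportive comparison.** Normal centre means with t-based intervals, 20 centres, groups of 8/6/6. Tight balance means keeping the 10% of grouped allocations best balanced on the rate (3,000 replicates); grouping only means no further restriction (1,500 replicates). The width ratio is for tight balance; type I error is two-sided, nominal 5%.

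| r | Width, with / without rate | Type I without rate, tight | Type I without rate, grouping only | Type I with rate (tight; grouping only) |
|---|---|---|---|---|
| 0 | 1.00 | 4.8% | 4.1% | 4.8%; 4.6% |
| 0.5 | 0.91 | 3.0% | 3.7% | 4.7%; 4.5% |
| 0.7 | 0.81 | 1.8% | 2.4% | 4.7%; 4.6% |
| 0.9 | 0.66 | 0.4% | 1.5% | 4.5%; 5.1% |

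A larger run of 20,000 trials per setting gives, without the rate, 5.1%, 3.2%, 1.8% and 0.5% under tight balance and 5.0%, 3.7%, 2.6% and 1.1% with grouping only; with the rate it gives 4.8 to 5.3%. In that run, omitting the rate overstates the standard error by about 0%, 8-11%, 16-24% and 32-52% at the four values of r.

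**6. The primary test, same simulations.** Under tight balance at r = 0.5, 0.7 and 0.9, the test on the restricted reference set has type I error of 4.5 to 5.0%. Its power is 80%, 89% and 97%, against 76%, 79% and 82% for a test that ignores the restriction. Adjusting its statistic for the rate again gives 80%, 89% and 97%. With grouping only, its power is 80%, 87% and 93%, and adjustment gives 83%, 90% and 97%, a gain of about 2 to 4 points.

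**The case against.** The case against is substantial, and most of it limits the point rather than removing it.

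- **The list is open and the article is condensed.** The covariates are given as examples, the sentence concerns their bearing on the intervention effect, and no full model specification is set out. This is fair. But the examples illustrate a stated class, patient-level covariates, and a centre's historical rate lies outside it.
- **The model does not omit every balancing factor.** Comorbidity, stage and regimen appear in both sections, and patient covariates may absorb part of the between-centre variation. This stands, and it may make the loss smaller than simulated.
- **The size rests on r.** The historical data cover diagnoses to mid-2013 and the protocol version is dated December 2016, so a high correlation is not assured. At r = 0 nothing is lost. This stands too, although choosing the rate as the grouping variable suggests it was expected to be prognostic.
- **The simulations are not the planned model.** They use normal centre means, not a negative binomial mixed model fitted to patient counts. They show direction and approximate size only.
- **The harm is limited.** The error is conservative, falls on a supportive analysis, and cannot change the primary p-value or interval.

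A reader might go further and infer that the primary test also ignores the historical rate. The protocol does not support that. The test and its interval use the restricted randomization distribution, and the rate helps define that reference set. The article describes no adjustment of the test statistic, but it does not give the statistic in full either, and adjustment would gain only about 0 to 4 power points in the settings examined.

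**Conclusion.** The point holds for the supportive model only. The variable on which centres were grouped is not among the covariates named for it, nor in the class from which they are drawn. If the historical rate is prognostic, the model's interval is too wide and its type I error is below nominal. With the rate included, the interval would be about 9% narrower at r = 0.5, 19% at r = 0.7 and 34% at r = 0.9, with no change at r = 0. Two-sided type I error without it is about 5%, 3%, 2% and 0.5% at r = 0, 0.5, 0.7 and 0.9 under tight balance, and closer to nominal with grouping alone for r above zero.

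The direction follows from the design; the size rests on the undocumented r, the assumed tightness of balance and the cluster-mean approximation. The primary randomization test is valid as described. This is an inexpensive improvement to a secondary line of evidence, not a threat to the trial's main conclusion.

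**What to change.** State that the supportive negative binomial mixed model will include the centre's 2010-2013 mean ED + H visits per patient as a fixed effect, either continuous or as the randomization group, and that the treatment effect will be tested with between-centre degrees of freedom. Leave the primary randomization test and its interval as they are.

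Twenty centres in two arms leave 18 between-centre degrees of freedom. The continuous form costs one (17 left); the group form costs two (16 left) if there are three groups as inferred. The data were already used for the allocation, so nothing new has to be collected. If the rate proves uninformative, the loss is about 1% of interval width or less for the continuous form.

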### Patient reported outcomes sub-study

A sub-set of approximately 25 consecutive, consenting patients enrolled at each participating centre take part in a PRO sub-study to assess the effect of the telephone intervention versus control on secondary outcomes. Severity of treatment side effects is measured using the National Cancer Institute Patient Reported Outcomes version of the Common Terminology Criteria for Adverse Events [26, 27] self-report tool, a symptom severity index, and by the Edmonton Symptom Assessment System [28] already collected routinely in patients in regional cancer programs throughout Ontario. Self-efficacy or confidence in managing symptoms is measured using the Stanford Self-Management Self-Efficacy Scale, and general quality of life by the EQ-5D-3 L. [29] The Patient Health Questionnaire [30] and Generalized Anxiety Disorder [31] scales are used to evaluate major depression and anxiety, respectively. The Functional Assessment of Cancer Therapy-Breast scale [32] is used to evaluate physical, social and family wellbeing for breast cancer patients. Coordination and continuity of care is measured using the adapted Picker survey [33, 34]. Lastly, self-care during chemotherapy is assessed using the Leuven questionnaire (L-PaSC) [35].

Participants are required to complete the PRO questionnaires prior to the start of the first (baseline) and second cycles of chemotherapy, and within 60 days of the end of treatment. For patients receiving a chemotherapy regimen where they switch to a different drug part way through (usually addition of a taxane), there is an additional PRO collection prior to the start of the second cycle of the second drug except for the L-PaSC questionnaire which is only completed prior to second cycle of chemotherapy and within 60 days of the end of treatment. Questionnaires completed by patients participating in the PRO sub-study will be linked to administrative data housed at ICES using the Ontario Health Insurance Plan (OHIP) numbers provided by individually consenting patients.

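### Neither of the two unranked PRO models is said to include the patient's own baseline score; a baseline-adjusted model should be named as the main PRO analysis

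*Protocol article*

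**What the plan says.** The Statistical analysis section of the protocol article assigns the PROs to general linear mixed models that allow for clustering within centres. They are to "assess the impact of the intervention alone, and after adjusting for important patient-level baseline covariates". That makes two analyses. The article does not say which is the main one and does not list the covariates of the second.

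The same section names covariates once, for the supportive negative binomial model of emergency department visits and hospitalizations (ED + H): "patient-level baseline covariates, such as age, stage, comorbidities, socioeconomic status and treatment regimen".

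Under Patient reported outcomes sub-study, participants are to "complete the PRO questionnaires prior to the start of the first (baseline) and second cycles of chemotherapy", and again within 60 days of the end of treatment. Patients who switch drug have one further assessment. The L-PaSC is the exception: read literally, it is completed only before cycle 2 and at the end of treatment, so it has no baseline.

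On size, the Sample size section says that "at least 25 patients per centre (total sample size: 500) need to be enrolled for 80% power" at a one-sided alpha of 2.5%, "to detect a treatment effect size of 0.35 standard deviations".

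**The concern.** A follow-up score's own baseline is usually its strongest single predictor. Here it is collected for nearly every scale, yet the article gives it no role in the analysis. The analysis stated first has the intervention alone.

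Two things are at stake. The first is precision: a comparison of follow-up scores carries between-patient variation that the baseline score would explain.

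The second is imbalance. Centres were allocated as whole units, whereas PRO patients give individual consent at their centre. Intervention-centre nurses are trained and make the calls, and control centres are denied the materials, so the arm is in practice known when consent is sought. The article does not state this; it follows from the design. The constrained randomization balanced centre characteristics from historical data. It cannot balance who agrees to complete questionnaires.

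**Working it through.** **Inputs from the protocol article.** 20 centres, 10 per arm (Statistical analysis); 25 PRO patients per centre, effect 0.35 SD, one-sided alpha 2.5%, stated power 80% (Sample size). The only ICC given is 0.028: "The intra-class correlation for the top-25 cohort was estimated at 0.028". It was estimated for ED + H visits and is borrowed here, because no PRO ICC is stated.

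**Assumed inputs.** The correlation r between baseline and follow-up score within patients is not in the article; 0.3, 0.5 and 0.7 are used. The centre-level correlation rc is set to 0 in the main calculation and to r as an upper case.

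**Formulas**, in SD units with m patients per centre:
- variance of a centre mean: V = ICC × (1 − rc²) + (1 − ICC) × (1 − r²)/m
- standard error of the arm difference: SE = √(2V/10)
- noncentrality: 0.35/SE; power from the noncentral t with 20 − 2 = 18 df, critical value 2.101

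**Step 1: the plan's own figure, without baseline.** V = 0.028 + 0.972/25 = 0.06688. SE = √0.013376 = 0.1157. Noncentrality = 3.026. Power = 81.6%, within two points of the stated 80%. The t calculation gives exactly 80% at an ICC of 0.031.

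**Step 2: add the baseline score, rc = 0, m = 25.**

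| r | V | SE | Noncentrality | Power | Effect detectable at 80% power |
|---|---|---|---|---|---|
| none | 0.06688 | 0.1157 | 3.026 | 81.6% | 0.343 SD |
| 0.3 | 0.028 + 0.03888 × 0.91 = 0.06338 | 0.1126 | 3.109 | 83.6% | 0.334 SD |
| 0.5 | 0.028 + 0.03888 × 0.75 = 0.05716 | 0.1069 | 3.273 | 87.2% | 0.317 SD |
| 0.7 | 0.028 + 0.03888 × 0.51 = 0.04783 | 0.0978 | 3.579 | 92.2% | 0.290 SD |

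If centre means are correlated to the same degree (rc = r), power is 85.1%, 91.0% and 97.9%. The gain therefore runs from about 2 to about 16 points.

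**Step 3: sensitivity to the borrowed ICC and to missed assessments** (rc = 0; ICC 0.04 and 20 evaluable per centre are assumptions).

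| ICC | m | No baseline | r = 0.3 | r = 0.5 | r = 0.7 |
|---|---|---|---|---|---|
| 0.028 | 20 | 76% | 79% | 83% | 90% |
| 0.04 | 25 | 75% | 77% | 81% | 86% |
| 0.04 | 20 | 70% | 73% | 77% | 83% |

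**Step 4: bias from baseline imbalance.** If the arms differ by b SD at baseline, an unadjusted follow-up comparison is off by about b × r. With b of 0.1 to 0.2 SD (assumed), this runs from 0.1 × 0.3 = 0.03 SD to 0.2 × 0.7 = 0.14 SD. Against the 0.35 SD target that is 0.03/0.35 = 9% to 0.14/0.35 = 40%.

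**The case against.** The strongest reply is that the article is silent on the baseline score and does not rule it out. A pre-cycle-1 score is itself a patient-level baseline covariate, so the second model may include it. Baseline could also enter a mixed model as a repeated outcome. An article commonly leaves the exact covariate list to the full protocol or analysis plan, neither of which is shown. This stands. A reader might infer that the PRO models omit the baseline score; the article does not say so.

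Nor does the list of age, stage, comorbidities, socioeconomic status and regimen show an omission. It belongs to the ED + H model and is introduced as examples.

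A reader might also infer that the sub-study is underpowered without adjustment. It is not, if the ED + H ICC carries over and 25 patients per centre are evaluable. Power falls below 80% only under a higher ICC or missing data, and both are assumptions.

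Three further limits stand:
- Baseline adjustment reduces bias from selective consent but does not remove it, since it handles only what the score captures. The article reports no imbalance and asks for consecutive consenting patients.
- The article specifies no normal cut-off for the PRO tests, so an inflated error rate from ignoring the small number of centres cannot be charged to it.
- Baseline self-efficacy is a doubtful stand-in for the missing L-PaSC baseline. Intervention patients receive the self-management booklet before chemotherapy, and its order relative to the baseline questionnaire is not stated.

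What the reply does not meet is that an intervention-alone analysis is written into the plan, stated first, and on equal footing with a loosely described adjusted one.

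**Conclusion.** The point holds as a recommended improvement to a stated analysis of secondary outcomes; it is not an error in a stated figure. The article leaves two PRO analyses unranked and gives the collected baseline score no stated role.

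At ICC 0.028 and 25 patients per centre, naming a baseline-adjusted main model is worth about 2, 6 or 11 points of power for r = 0.3, 0.5 or 0.7 with no centre-level correlation, and more with it. At r = 0.3 the gain is small. The model also offers partial protection against a baseline difference, which could otherwise shift the estimate by 0.03 to 0.14 SD under the assumed imbalances.

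The sizes rest on assumed correlations, an ICC borrowed from another outcome and assumed imbalances. The direction does not depend on the particular values, provided baseline and follow-up scores are correlated.

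**What to change.** For each PRO scale with a baseline, name as the main analysis a linear mixed model of the follow-up scores with arm, time, arm-by-time, that scale's baseline score and a random centre effect. Use small-sample degrees of freedom, for example Kenward-Roger. Report the intervention-alone model as secondary. Leave the L-PaSC without a baseline-score covariate and say why. If the analysis plan already specifies such a model, it is enough to confirm that it is the main one.

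The cost is analysis-plan wording, settled before the PRO data are compared by arm. No new data, patients or visits are needed.

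### Imputing missed patient-reported outcomes centre by centre, with about 25 patients each, overstates the standard error of the arm difference and costs the sub-study power

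*Protocol article*

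**What the plan says.** The Statistical analysis section plans this model for the PROs: "Patient reported outcomes will be assessed using general linear mixed models to adjust for clustering of the individuals within centres". The arm effect is to be estimated alone and then adjusted for patient covariates. One sentence deals with missing questionnaires: "Multiple imputation within centres will be used to account for missed assessments".

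The Patient reported outcomes sub-study section gives the size of each centre's data: "A sub-set of approximately 25 consecutive, consenting patients enrolled at each participating centre take part in a PRO sub-study". The Sample size section requires at least 25 per centre, 500 in total, for 80% power at one-sided 2.5% "to detect a treatment effect size of 0.35 standard deviations". There are 20 centres, 10 per arm. The only ICC in the article concerns emergency department visits and hospitalizations: "The intra-class correlation for the top-25 cohort was estimated at 0.028".

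The article gives no expected missing rate, PRO ICC or imputation predictors. These may stand in the full protocol or analysis plan, and their absence is not the point here.

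**The concern.** Respecting centre in the imputation is sound, because ignoring it would understate the SE. The difficulty is doing it with each centre on its own. With 10-20% missing, a centre's imputation model rests on about 20-22 observed patients, and it must estimate its own intercept, slopes and residual variance without borrowing from other centres.

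The resulting noise enters each centre's completed mean. With 10 centres per arm, the SE of the arm difference comes from the spread of those means, so the noise inflates it once. Rubin's rules then add the same noise again as between-imputation variance. The planned mixed model treats centres as draws from a common distribution, and the imputation model does not.

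At stake is the sensitivity of the PRO comparisons. The 500 patients are justified by power alone, with no stated allowance for missing data.

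**Working it through.** **1. The plan's own figure.** For 0.35 SD, one-sided 2.5% and 80% power: n per arm = 2(1.96 + 0.84)²/0.35², which rounds up to 129, or 258 in total. Assume the ICC of 0.028 carries over to the PROs. The design effect is then 1 + 24 × 0.028 = 1.672, and 258 × 1.672 = 431. At 500 patients, power is 85.7% by the normal formula and 81.6% by noncentral t with 18 df. The normal formula gives exactly 80% at an ICC of about 0.0396. The planned size is reproduced, with little reserve.

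**2. Size of the double counting in the simplest case.** Let each centre have n = 25 patients, a fraction m missing, between-centre variance τ² and within-centre variance σ² (τ² + σ² = 1). Impute from the centre's own mean, with no predictors and many imputations. Put a = σ²/[n(1 − m)].
- True variance of a centre's mean: τ² + a.
- Spread of completed centre means within one imputed data set: τ² + a(1 + m).
- Between-imputation variance of a centre's mean: a·m.
- Variance reported by Rubin's rules, per centre: τ² + a(1 + 2m).

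SE ratio (reported/true) = √{[τ² + a(1 + 2m)]/[τ² + a]}.

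With ICC 0.028 and m = 0.2: a = 0.972/20 = 0.0486, so the ratio is √(0.0960/0.0766) = 1.12. With m = 0.1: a = 0.0432, and √(0.0798/0.0712) = 1.06. The ratio falls towards 1 as τ² grows, so the problem belongs to small ICCs.

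**3. Simulation with predictors.** Set-up: 20 centres × 25 patients, 600 trials per setting, 10 imputations. Missingness was at random given a covariate correlated 0.5 with the outcome. The analysis was an unadjusted random-intercept model by REML, with Rubin's rules and Barnard-Rubin df (complete-data df 18). The table is for ICC 0.0397, where complete-data power was 74-77%.

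| Missing | Predictors | SE ratio: separate / fixed centre / random intercept | Power %: separate / fixed centre / random intercept / no imputation |
|---|---|---|---|
| 10% | 1 | 1.07 / 1.07 / 1.02 | 69.2 / 70.0 / 72.8 / 73.2 |
| 10% | 5 | 1.09 / 1.05 / 1.01 | 67.8 / 70.7 / 74.3 / 74.3 |
| 10% | 10 | 1.12 / 1.06 / 1.01 | 62.3 / 70.7 / 74.3 / 73.7 |
| 20% | 1 | 1.12 / 1.09 / 1.00 | 62.2 / 63.2 / 70.5 / 69.7 |
| 20% | 5 | 1.16 / 1.10 / 1.00 | 52.5 / 64.3 / 69.7 / 70.8 |
| 20% | 10 | 1.40 / 1.07 / 0.98 | 38.9 / 65.3 / 72.3 / 71.2 |

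The loss from separate imputation relative to the random intercept runs from 72.8 − 69.2 = 3.6 to 74.3 − 62.3 = 12.0 points at 10% missing. At 20% missing it runs from 70.5 − 62.2 = 8.3 to 72.3 − 38.9 = 33.4 points. The Monte Carlo error of one power figure is about √(0.7 × 0.3/600) = 1.9 points.

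At ICC 0.01 the SE ratio for separate imputation was 1.10-1.19 (10% missing) and 1.17-1.54 (20%). Power at 20% missing was 75/66/46% with 1/5/10 predictors, against 84-86% with a random intercept.

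The top of the range needs 10 predictors. In the 20% row, the tabulated SEs of 0.1812 (reported) and 0.1529 (true) have ratio 1.19, against the quoted 1.40. That gap is consistent with a minority of nearly saturated centre fits producing very large SEs.

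**4. Second simulation.** Cluster means, ICC 0.01-0.03 and 10-20% missing gave SEs 2-49% too large with separate imputation and 1-30% too large with fixed centre effects. Available-case cluster means had ratios of 0.94-1.13.

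**5. Can the centre models be fitted?** With up to 10 continuous predictors and up to 20% missing, at most 0.2% of trials had a failure. With 13 parameters (the covariates named for the primary outcome's supportive model, "such as age, stage, comorbidities, socioeconomic status and treatment regimen", plus two earlier PRO scores; level shares assumed), at least one centre failed in 80-100% of trials.

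**The case against.** The strongest reply is that *within centres* may only mean that the imputation respects clustering, as the neighbouring sentence on the mixed model does. If a random centre intercept is intended, nothing is wrong: its SE ratios were 0.98-1.05 throughout. That reading is possible, but the words more naturally describe imputing inside each centre. The milder reading, fixed centre effects with common slopes, still overstates the SE.

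It is also fair to say that the size of the loss rests on assumptions, and that with 10% missing and few predictors it is only about 4-7 points.

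Three stronger conclusions that a reader might draw are not supported:
- **That the imputation often cannot be run.** This depends on an imputation model that the article does not give. The covariates used in the unfavourable case are listed for the negative binomial model of the primary outcome, not for PRO imputation.
- **That imputation adds nothing to a likelihood analysis.** The mixed model is valid under missing at random given what is in the model, and the first PRO analysis has the intervention alone. Imputation can use auxiliary information, such as the routinely collected symptom scores.
- **That planned power of 80% falls to a definite figure such as 59%.** That figure rescales an assumed 80% in one chosen scenario.

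**Conclusion.** The point stands as an inexpensive improvement, not as a defect that must be corrected before the trial can be interpreted. Under both separate-centre and fixed-centre imputation the SE of the arm difference is overstated when the ICC is small. For separate-centre imputation the excess is roughly 2-20% at 10% missing and 10-50% at 20%, with a power loss of about 4-12 and 8-33 points relative to random-intercept imputation. With fixed centre effects the loss at ICC 0.0397 is about 3-4 and 5-7 points.

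These figures assume 25 patients per centre, a PRO ICC of 0.01 to 0.04, 1 to 10 predictors and data missing at random. The SE-ratio ranges draw on both ICCs and both simulations; the power losses are at ICC 0.0397.

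The error is conservative: intervals are too wide, and false positives are not inflated. The primary outcome, which comes from administrative data and is tested by randomization, is unaffected.

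**What to change.** Replace the imputation sentence by one of two equally acceptable statements.

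(a) PROs will be analysed with the planned linear mixed model, fitted by REML to all available assessments and including the baseline score, under missing at random.

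(b) Missed assessments will be multiply imputed with a multilevel model that has a random centre intercept, with slopes and residual variance pooled across centres, run by arm, compatible with the analysis model and able to include auxiliary variables.

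At 20% missing and ICC 0.0397 the two performed alike: 70-71% power without imputation and 70-72% with random-intercept imputation. Option (a) is simpler; option (b) is preferable if useful auxiliary variables exist.

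The cost is small. Slopes are assumed common across centres, and only analysis wording changes; data collection and sample size do not.
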